### Data collection and management

Research data will be collected in the following forms: (1) Electronic data, which participants will directly input, will be encoded and stored securely in an online database and subsequently transferred to the study database by the research team; (2) paper-and-pencil forms, which will be collected and manually entered into the study database by the trial therapist.

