### Trial design

This is a single-university, assessor-blinded, parallel, 2-arm, block randomized (1:1) controlled superiority trial for female university students exhibiting high levels of RNT, conducted in Nara, Japan. To maintain a 1:1 allocation ratio between the two arms, block randomization will be applied, with each set of two participants randomized to one of the two conditions.

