### Randomization and concealment

Participants will be randomly allocated to either the RFCBT guided self-help intervention group or waitlist control group in a 1:1 ratio. Randomization will be concealed from the investigators by use of an off-site, computer-based randomization. To maintain a 1:1 allocation balance, block randomization will be employed, such that every two participants are randomly allocated to either the intervention or waitlist condition. All assessments will be conducted by researchers who are blinded to the randomization process. Assessor blinding will be ensured by administering all assessments online and by avoiding any in-person contact with participants after randomization. Follow-up reminders will be systematically scheduled and disseminated in an identical manner across both groups.

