### Outcome measures

#### Primary outcome measure: Rumination

The RRS [55] is a 22-item self-report measure designed to assess the frequency of depressive rumination on a 4-point scale (1: Almost Never to 4: Almost Always). The Japanese version has demonstrated sufficient internal consistency (Cronbach’s α = 0.93), test–retest reliability (*r* = 0.75 over a 6-week period), as well as factorial and concurrent validity (*r* = 0.56–61 with PSWQ, depression [68]), and self-preoccupation [69] scales) [62], and has shown measurement invariance with the original version [70]. The total score across the 22 items will be used as the primary outcome measure. A higher score reflects a greater propensity for rumination.

Additionally, we will use the two subscale scores, i.e., brooding and reflective pondering, as secondary outcome measures, each comprising 5 items from the RRS [55]. Hasegawa [62] reported Cronbach’s α = 0.81 for brooding and α = 0.75 for reflective pondering.

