#### Secondary outcome measures: Worry, depression, and anxiety

In addition to brooding and reflective pondering, the following self-report measures will be used as secondary outcome measures.

The PSWQ [56] is a 16-item self-report measure that assesses the respondent’s tendency for worry on a 5-point scale (1: Not at all typical of me to 5: Very typical of me). The Japanese version has demonstrated sufficient internal consistency (Cronbach’s α = 0.92), test–retest reliability (*r* = 0.88 over a 2-week period), and concurrent validity (*r* = 0.72 with State-Trait Anxiety Inventory [STAI]-Trait [71]]) [63]. The total score across the 16 items will be used. A higher score reflects an increased propensity for worry.

The PHQ-9 [57] measures the frequency of depressive symptoms over the past two weeks on a 4-point scale (0: Not at all to 3: Nearly every day). The Japanese version has shown high sensitivity and specificity (between 0.84 and 1.00), as well as high convergent validity (Kappa coefficientκ = 0.79 for diagnosis of major depressive disorder) [72]. The total score of the 9 items will be used. A higher score indicates greater severity of depressive symptomatology.

The Generalized Anxiety Disorder-7 (GAD-7; [58]) assesses the frequency of anxiety symptoms over the past two weeks on the same 4-point scale as the PHQ-9. The Japanese version has demonstrated sufficient sensitivity and high specificity (with a cutoff score of ≥ 10 yielding a sensitivity of 70.6% and specificity of 93.5%,[73]), as well as high concurrent validity (*r* = 0.74 with STAI [71]]; [74]), reflecting robust construct validity. The total score of the 7 items will be used. A higher score reflects increased severity of anxiety.

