#### Process measures: RNT and alternative responses as habits

Two self-report measures are incorporated to assess the habitual tendency for rumination and the use of alternative processing modes. To evaluate the habitual tendency for rumination, we will include 12 items from the Habit Index of Negative Thinking (HINT; [75]), translated by the authors for this study. Additionally, the 9 items from the HINT were selected to constitute a separate measure assessing participants’ habitual use of alternative coping strategies.

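### The trial is labelled assessor-blinded, but every outcome is self-reported by participants who know their arm, so the label does not protect the primary result

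*Protocol article*

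**What the plan says.** **Label.** The abstract, the section The current study, Trial design and the Discussion all describe the trial as assessor-blinded. Trial design reads: "This is a single-university, assessor-blinded, parallel, 2-arm, block randomized (1:1) controlled superiority trial".

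**Mechanism.** Randomization and concealment says "All assessments will be conducted by researchers who are blinded to the randomization process", and then "Assessor blinding will be ensured by administering all assessments online and by avoiding any in-person contact with participants after randomization". It adds that reminders are sent in the same way to both groups.

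**Outcomes.** The RRS "is a 22-item self-report measure designed to assess the frequency of depressive rumination on a 4-point scale"; brooding and reflective pondering are subscales of it. For the PSWQ, PHQ-9 and GAD-7, the text says that "the following self-report measures will be used as secondary outcome measures". For the HINT-based items: "Two self-report measures are incorporated to assess the habitual tendency for rumination and the use of alternative processing modes".

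**Knowledge of allocation.** Under Screening and consent procedure, the trial therapist tells each participant her group. Under Waitlist control, the comparison group waits 8 weeks for the same programme. Under RFCBT guided self-help, the therapist meets participants face to face after each workbook.

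**Data flow.** Data collection and management describes two streams: electronic data typed in by participants, and paper forms, "which will be collected and manually entered into the study database by the trial therapist".

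**Limitations.** Strengths and limitations covers the single-case origin of the earlier evidence, possible harm from a waitlist, short follow-up, low power for the latent growth models and the single site. Unblinded self-report is not listed.

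**The concern.** Blinding the assessor helps when a person other than the participant makes a judgement that knowledge of the arm could sway. Here the participant makes every rating, and she knows whether she has received the programme or is waiting for it. The headline design feature therefore describes a protection that no outcome receives.

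The conclusions lean on it. The Discussion says the waitlist comparison will separate effects specific to the intervention from natural improvement and regression to the mean. Strengths and limitations says it will show whether the observed effects are real therapeutic benefit. A waitlist does address passage of time and repeated measurement, as The current study notes. It does not address expectation, or a wish to report progress to a study whose therapist one meets repeatedly. A reader who sees the label and no matching limitation may give the primary result more weight than the design supports.

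The data-entry route is a separate loose end. If any outcome were captured on paper, the stated basis for blinding would fail for that outcome, and the person keying it would know the arm.

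**Working it through.** **Step 1. Who rates each outcome?**

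| Measure | Role | Rater | Rater blind to arm? |
|---|---|---|---|
| RRS total | primary | participant | no |
| Brooding | secondary | participant | no |
| Reflective pondering | secondary | participant | no |
| PSWQ | secondary | participant | no |
| PHQ-9 | secondary | participant | no |
| GAD-7 | secondary | participant | no |
| HINT items, rumination habit | process | participant | no |
| HINT items, alternative coping | process | participant | no |

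Primary and secondary scores: 1 + 5 = 6. With the two process measures: 6 + 2 = 8. Measures with a blinded rater: 0 of 8.

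**Step 2. What is the blinding said to rest on?** Randomization and concealment gives two supports.

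- *All assessments online.* Data collection and management also provides for paper research data. Either the paper forms hold no outcomes, and the text should say so, or they do, and the two sections contradict each other.
- *No in-person contact after randomization.* The therapist does hold in-person sessions. The phrase fits with this only if it refers to assessment staff, which is the natural reading but is not spelled out.

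The same section calls the researchers blind to the randomization process. That is closer to allocation concealment than to being unaware of a participant's arm.

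**Step 3. The plan's own figures, reproduced.** Inputs from Sample size estimation: mean changes 16 and 5, SD 14.5, two-sided 5%, power 90%, dropout 23%.

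- Effect size: (16 − 5)/14.5 = 0.759; the plan uses 0.75.
- Two-sample t-test (noncentral t) at d = 0.75: n = 38.35, so 39 per arm, with power 0.905.
- Dropout: 39/(1 − 0.23) = 50.6, so 51 per arm and 102 in total.

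The stated sample size is reproduced, and this point does not change it.

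**Step 4. Illustration of what is at stake.** The document gives no size for reporting bias, so a range is assumed. Suppose there is no true effect, 39 are evaluable per arm, and reports differ between arms by b SD from expectation alone. The test statistic then has 2 × 39 − 2 = 76 degrees of freedom and noncentrality b × √(39/2). The chance of a significant two-sided result is:

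| Assumed b (SD) | RRS points (b × 14.5) | Rejection rate |
|---|---|---|
| 0.1 | 1.45 | 7.2% |
| 0.2 | 2.90 | 14.1% |
| 0.3 | 4.35 | 25.8% |
| 0.4 | 5.80 | 41.5% |
| 0.5 | 7.25 | 58.7% |

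The nominal rate is 5%. The table shows sensitivity to an assumed bias and is not an estimate for this trial. It uses a plain t-test on change, as the sample size does, not the covariate-adjusted model planned for the analysis.

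**The case against.** The best defence is that the document is candid about each ingredient. It calls the outcomes self-reported in the hypotheses, says that allocation is disclosed, and nowhere claims that participants are blinded or that expectation effects are controlled. Online administration and identical reminders give a real, limited protection against staff prompting one arm differently. Participants cannot be blinded to a waitlist, and the article already concedes, on other grounds, that the waitlist is a weak comparator.

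Most of this stands. It shows that the design is conventional and that the procedures are worth describing. It does not show that the label protects any outcome rating, and it does not supply the missing limitation. Nor can brevity explain the gap: the article itself states the label, its mechanism and the data-entry route.

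Four stronger readings are tempting, and the document does not support them.

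- *Therapist entry biases the RRS.* The data section never says that the paper forms carry the RRS or any other outcome. They could hold workbook material.
- *Any such bias falls on the intervention arm only.* Paper forms are not limited to one arm.
- *The therapist's sessions break assessor blinding.* The no-contact sentence follows one about assessors and can be read as covering them alone.
- *The size of the bias is known.* It is not; the rates in the working follow from assumed values.

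**Conclusion.** The point holds as one about a stated design property that the trial lacks. None of the six primary and secondary scores and neither process measure has a blinded rater, so the assessor-blinded label does not protect the primary result from expectation or reporting bias. The limitations section omits this while the conclusions depend on it. This rests only on what the article says about self-report, disclosure of allocation and the waitlist.

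The mismatch between fully online assessment and paper forms entered by the therapist is real and needs reconciling, but it is a possible route to bias and not an established one. The amount of reporting bias cannot be derived from the document. The matter should be corrected, but it does not invalidate the randomized comparison or alter the sample size.

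**What to change.** 1. In the abstract, The current study, Trial design and the Discussion, describe the trial as open-label with participant-reported outcomes. Online administration and identical reminders in both arms can still be described as procedures.
2. Reconcile Randomization and concealment with Data collection and management. Either confirm that no primary or secondary outcome is collected on paper, or have any paper outcome form entered by existing staff confirmed blind to allocation instead of the therapist. The article does not show that the trial manager is blind, so naming that role would not be enough by itself. State also that the no-contact rule applies to assessment staff, if that is meant.
3. Give the statistician coded arms until the primary model is locked. Claim analyst blinding only if this is done; the article does not currently state it.
4. Add unblinded self-report to Strengths and limitations. Temper the statements there and in the Discussion that the waitlist comparison will establish real therapeutic benefit or effects specific to the intervention.

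The cost is wording, a coded dataset and perhaps a minor reassignment of data entry. The downside is a less favourable design label. Sample size, schedule and treatment are unchanged.

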#### Interim analysis

Interim analysis will be performed on the primary and secondary outcome measures when 50% of participants have been randomized and have completed the 8-week follow-up. The interim analysis will be conducted by the DSM officer. Results of the interim analysis will be reported to the authors. The authors will discuss the results of the interim analysis, and decide on the continuation of the trial. The trial may be stopped or modified following inflated risk, as indicated by significant increases in scores of outcome measures or specific risk items (e.g., depression, risk of self-harm/suicide).

#### Confidentiality

All study-related data will be securely stored either at the study site or within a protected database. Participants’ information will not be disclosed outside the study without their written permission.

### Ethical considerations and trial pre-registration

The research protocol received approval from the institutional review board of the first author’s affiliated university (approval number 23–32, approved October 26th, 2023; latest version: approval number 25–79, approved December 25th, 2025). This trial has been registered with the jRCT (jRCT1050240305) (initially pre-registered with the UMIN-CTR [UMIN000053430]). Recruitment commenced in January 2024. If significant modifications to the protocol arise, they will be conveyed through amendments to the registered trial information.

## Discussion

RFCBT employs a functional analytic framework to directly intervene on rumination with the aim of shifting individuals toward more adaptive modes of processing [14]. RFCBT has demonstrated its efficacy across multiple randomized controlled trials [31, 33, 38, 39, 41],however, most trials have been conducted within Western populations. Efforts to adapt RFCBT for distinct cultural contexts while maintaining high fidelity to its foundational principles remain limited.

Accordingly, this single-site, assessor-blinded, parallel, two-arm, block randomized controlled trial seeks to evaluate the effectiveness of a culturally adapted version of RFCBT delivered in a guided self-help format using printed workbooks. We selected Japanese female university students as our target population, given their elevated risk for mental health difficulties [8, 54], and our intention to examine the cross-cultural generalizability of RFCBT. The intervention comprises four workbooks, each incorporating core components of RFCBT: self-monitoring and functional analysis, concreteness, compassion, and absorption. Intervention effects will be evaluated relative to a waitlist control group, enabling us to distinguish intervention-specific effects from spontaneous improvement or regression to the mean.

This study offers a unique opportunity to examine the efficacy of RFCBT in a culturally adapted format within a population whose cultural background differs from those previously studied and for whom intervention effects remain unknown, thereby yielding important clinical implications. Furthermore, evidence supporting the effectiveness of the culturally-adapted RFCBT will substantiate and validate the rigor of our cultural adaptation process.

If rumination is substantially reduced among participants following the intervention relative to the waitlist control, this will indicate that the culturally-adapted RFCBT is an effective intervention for addressing rumination in Japanese female university students. Given the established associations between rumination and both depression and anxiety, demonstrating reductions in rumination would further support RFCBT as a promising intervention and prevention approach for these conditions among Japanese female young adults.

Reductions in RNT following RNT-focused cognitive-behavioral interventions are associated with symptomatic improvement [34, 35]. However, empirical evidence demonstrating that symptom reduction is a consequence of diminished rumination remains limited [35]. The present study will advance theoretical understanding of rumination as a central risk factor for depression and anxiety by examining its role as a psychopathological mechanism that exerts a causal influence on these conditions.

Additionally, it is crucial to explore whether RFCBT can be effectively delivered as a guided self-help intervention through a workbook format. Although RFCBT has been administered via guided online self-help formats [38, 78], no study has yet examined its effectiveness in a workbook format. This study aims to evaluate the effectiveness of this previously untested mode of delivery.

### Strengths and limitations

This study has several limitations. Although RFCBT guided self-help has demonstrated promising results in reducing RNT as well as depressive and anxiety symptoms in Japanese samples, these findings were derived from single-case designs [45, 46]. To delineate true intervention effects from spontaneous improvement or regression to the mean, the present study therefore incorporates a waitlist control condition. While comparisons between the self-help and waitlist conditions enable us to ascertain whether observed effects reflect genuine therapeutic benefit rather than spontaneous remission, and although waitlist controls remain widely used in clinical trials evaluating psychological interventions [52], some evidence suggests that waitlist conditions may exert detrimental effects [53]. Accordingly, once intervention effects are established within our design, future studies may profit from employing no-treatment or non-specific control conditions.

Because our primary objective is to detect intervention-related change, this trial employs a pre-post design that assesses relatively short-term outcomes (4- and 8-week post-randomization). However, to determine whether reductions in RNT meaningfully protect participants from future depressive episodes, longer-term follow-up assessments are essential. Subsequent studies should evaluate whether treatment gains are sustained over extended periods following the termination of the intervention.

Third, our sample size was calculated based on expected between-group differences; thus, additional multivariate latent growth analyses are insufficiently powered. Fourth, the single-site design may increase the risk of sampling bias.

Despite these limitations, the study possesses notable strengths. To our knowledge, this is the first adequately powered RCT to evaluate the effectiveness of RFCBT in reducing RNT in a non-Western population. Prior to the trial, the content and delivery of the guided self-help program were refined and substantiated through preliminary case-series studies [45, 46], enhancing the likelihood that the intervention would be effective in our target population.

University students in Japan, as well as in other countries, are experiencing a mental health crisis. Demonstrating that high-risk students with elevated RNT can be effectively supported would represent a critical step toward improving the mental health of this vulnerable population.

## Data Availability

The datasets used during the current study will be available from the corresponding author on reasonable request.

## Abbreviations

RNT: Repetitive negative thoughts
CBT: Cognitive behavioral therapy
RFCBT: Rumination-focused cognitive behavioral therapy
RCT: Randomized controlled trial
DSM: Data and safety monitoring
NIMH: National Institute of Mental Health
RDoC: Research Domain Criteria
TAU: Treatment as usual
NICE: National Institute of Health and Clinical Excellence
RRS: Ruminative Responses Scale
PSWQ: Penn State Worry Questionnaire
PHQ-9: Patient Health Questionnaire-9
GAD-7: Generalized Anxiety Disorder-7
HINT: Habit Index of Negative Thinking
ITT: Intention-to-treat
MI: Multiple imputation
FIML: Full information maximum likelihood
jRCT: Japan Registry of Clinical Trials
NWU: Nara Women’s University
JSPS: Japan Society for the Promotion of Science
